## 2. Materials and Methods

We will perform an observational study using a retrospective test-negative case–control design. This method has been used successfully to estimate the effectiveness of vaccines against respiratory diseases such as influenza virus infection [25,26,27] and COVID-19 [28,29,30,31,32].

A test-negative study is considered a variant of the traditional case–control design: the study population is composed by individuals who have a predefined set of symptoms, seek help at the same healthcare unit and are tested by the same methodology, in this case, real-time reverse transcription polymerase chain reaction (rRT-PCR) or an antigen test for SARS-CoV-2. The cases are individuals who receive a positive result and controls are those with a negative result [2,33].

Patients with COVID-19-like illness admitted to the Hospital of Viana do Castelo and Hospital of Ponte de Lima from 1 June 2021 until 2 March 2022, will be enrolled. These hospitals serve a population of 231,293 people resident in the district of Viana do Castelo, located in the northern region of Portugal, as shown in Figure 2.

Patients will be eligible if they are aged 18 years old or above on the date of hospital admission, resident in the district of Viana do Castelo, meeting any of the WHO clinical criteria for COVID-19, namely acute onset of fever, cough, general weakness, fatigue, headache, myalgias, sore throat, coryza, dyspnoea, recent onset of anosmia or dysgeusia, anorexia, nausea, vomiting, diarrhoea or altered mental status who received rRT-PCR or antigen testing for SARS-CoV-2 within 10 days of illness onset.

Exclusion criteria include patients not eligible for vaccination against COVID-19 or without information on the vaccination status and without SARS-CoV-2 test results available.

Primary outcomes include (1) SARS-CoV-2 symptomatic infection, confirmed by rRT-PCR or antigen test in respiratory samples from the nasopharynx or oropharynx and (2) moderate–severe COVID-19 disease, defined by hospitalization for over 24h, intensive-care unit (ICU) admission or death.

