Baseline demographic and health data are going to be collected, namely age, gender, municipality of residence, date of vaccination and type of vaccine used, number of doses, previous SARS-CoV-2 infection, and being in a clinically extremely vulnerable group due to immunodepression or respiratory disease [34]. These variables are going to be studied as potential confounders, as they may influence both the receipt of the vaccine and the occurrence of COVID-19.

The results will be compared in two periods: 1 June to 31 September 2021, corresponding to the fourth pandemic wave in Portugal and 1 November 2021 until the 2 March 2022 (fifth pandemic wave). Vaccine’s roll-out was fast in Portugal, being 50% of people fully vaccinated by 20 July 2021. Moreover, on the 22 September 2021, Portugal was the first country in the world hitting the milestone of 85% of the population fully vaccinated [35]. Initially, COVID-19 vaccines were only approved for people older than 16 (Comirnaty) or 18 years old (the other vaccines approved in the UE/EEA). In Portugal, vaccination of adolescents between 12 and 15 years old begun in August and for children from 5 to 11 years old was only approved in December of 2021. Therefore, children and adolescents under 18 years will be excluded from this study.

Data analysis will be performed using R Statistical Package^®^, Vienna, Austria (SPSS), 4.1.0 version. We will perform a descriptive analysis of all variables obtained within the scope of this research project. For continuous variables with a symmetric distribution, the mean and standard deviation are going to be used; if the distribution is not symmetric, the median and interquartile range will be chosen. Categorical variables will be described as absolute and relative frequencies.

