The normal distribution of the data will be verified by visual inspection of the histogram and the Kolmogorov–Smirnov test. Baseline characteristics of cases and controls will be compared using the chi-square test, Fisher’s test, Student’s *t* test or Mann–Whitney U test, depending on the nature of the variable. The association between the vaccination status and baseline characteristics will be investigated for cases and controls. The analysis will be stratified according to age, gender, municipality of residence, date of onset of illness, date of vaccination, vaccine administered, previous SARS-CoV-2 infection, and criteria for belonging to extremely vulnerable groups [34]. The presence of interaction will be evaluated by comparing the odds ratio (OR) in the various strata for a given variable. The presence of confounding will be assessed by comparing the unadjusted and adjusted OR for each of the covariates.

Multivariate logistic regression models will be used to estimate the unadjusted and adjusted OR for each of the covariates described, considering possible confounders. Covariates were selected a priori based on their known associations with SARS-CoV-2 infection or severe disease and inoculation with a COVID-19 vaccine [33] and will be evaluated as potential confounders.

The vaccine effectiveness (EV) will be estimated from the vaccination odds ratio, adjusted for confounders (OR_ad_), between cases and controls, according to the following formula:OR = (1 − OR_ad_) × 100

The variables will be tested for multicollinearity. The presence of interaction will be verified through the likelihood test or Wald test and will be included in the model if they are significant for a significance level of 5%.

In a subsequent analysis, the vaccine effectiveness will be evaluated by the time since vaccination. The time since vaccination will be calculated by subtracting the test date from the last inoculation date. The time since vaccination will be modelled as a continuous variable.

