## 3. Results

On the 14 May 2022, the data collection was still ongoing, and it is expected to be completed by June 2022. A preliminary analysis is going to be performed after finishing data collection. Currently, we have obtained data on 1329 eligible patients (652 cases and 677 controls) for both periods of the study and we plan to increase the number by 30%. We expect to obtain a vaccine effectiveness of between 40 and 70% in the prevention of symptomatic infection and 70 and 90% in the prevention of severe cases of COVID-19, according to previously described results. It is anticipated that this effectiveness may be lower in more advanced age groups due to a less-robust response of the immune system in these individuals. Additionally, we expect lower vaccine effectiveness in unvaccinated or partially vaccinated people, particularly in people with moderate-to-severe COVID-19. As the waning of VE has been previously reported [36], we believe that VE will be lower in people vaccinated with their last dose first. However, data analysis will allow us to confirm this. The results will be disseminated in national and international scientific journals in 2022–2023.

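### Time since vaccination is subtracted in the wrong order, ends at the test rather than at onset, and runs from the last dose of any number without saying that the waning analysis is done by dose

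*Protocol article*

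**What the plan says.** All of this is in the protocol article, section 2 (Materials and Methods), unless noted.

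- The waning analysis is an additional one: "In a subsequent analysis, the vaccine effectiveness will be evaluated by the time since vaccination".
- Its time variable is defined explicitly: "The time since vaccination will be calculated by subtracting the test date from the last inoculation date".
- Its form is given in one sentence: "The time since vaccination will be modelled as a continuous variable". Linear, spline or single-term is not stated.
- Eligible patients are those "who received rRT-PCR or antigen testing for SARS-CoV-2 within 10 days of illness onset", so onset can precede the test by up to 10 days.
- Onset date is available, because it is a stratification variable: "The analysis will be stratified according to age, gender, municipality of residence, date of onset of illness, date of vaccination, vaccine administered". That list goes on to previous infection and vulnerability criteria. Number of doses is not in it.
- Number of doses is collected, in the list "date of vaccination and type of vaccine used, number of doses, previous SARS-CoV-2 infection", and of that list the article says: "These variables are going to be studied as potential confounders, as they may influence both the receipt of the vaccine and the occurrence of COVID-19".
- Section 3 (Results) shows the direction the investigators expect: "we believe that VE will be lower in people vaccinated with their last dose first".

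**The concern.** The definition has three separate weaknesses.

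1. **Order of subtraction.** Inoculation date minus test date is the negative of elapsed time. A slope fitted to it has the opposite sign.
2. **End point of the interval.** Protection against symptomatic disease is a matter of vaccination status at onset. Ending at the test lengthens the interval by the testing delay. It also lets a dose given between onset and test become the last dose, although it could not have prevented that illness.
3. **Starting point of the interval.** The clock restarts with each dose. In the second period (1 November 2021 to 2 March 2022), short times would be mainly recently boosted patients and long times mainly patients with two doses and no booster. Time and dose number are then correlated by construction. A slope that ignores dose number mixes the booster effect with waning.

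The Introduction asks whether boosters work and how long their effect lasts, and the Conclusions hope to inform booster decisions. A slope that mixes the two answers neither question cleanly. Because the investigators already expect waning, an artefact in that direction would look like confirmation.

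**Working it through.** The article gives no power, sample size or error rate for this analysis, so there is no figure to reproduce. Its counts agree: 652 + 677 = 1,329, and 1,329 × 1.3 = 1,727.7, or about 1,728.

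**Sign.** Take a hypothetical last dose on 1 June 2021 and a test on 15 January 2022.
- As written: inoculation minus test = −228 days.
- Reversed: test minus inoculation = +228 days.

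If the odds ratio truly rises by a factor of 1.10 per 30 days (waning), the variable as written returns 1/1.10 = 0.909, which reads as strengthening protection. Simulation agrees: 1.098 with the correct sign and 0.909 with the sign as written. With no waning, the reversed variable gives 1.000, so it creates nothing.

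**Simulation set-up for the next two checks.** There were 400 runs of N = 1,728, half in each period. The model was logistic with terms for vaccinated and vaccinated × time, and true waning within each dose was zero. The following inputs are assumptions, because the article does not give them:
- Period 1: 35/20/45% with 0/1/2 doses. Period 2: 12/3/45/40% with 0/1/2/3 doses.
- Dose 1 at 0–60 days. Dose 2 at 0–120 days (period 1) or 90–270 days (period 2). Dose 3 at 0–90 days.
- Vaccine effectiveness (VE) between the article's expected 40% and 70%.
- Two-sided 5% test, so false waning should appear in about 2.5% of runs.

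**Test date instead of onset** (VE 55% for every dose)

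| Mean delay, cases / controls | OR per 30 days | False waning | False strengthening |
|---|---|---|---|
| 3 / 3 days | 0.999 | 1.5% | 2.2% |
| 5 / 2 days | 1.016 | 11.5% | 0.7% |
| 2 / 5 days | 0.985 | 0.3% | 8.7% |
| 5 / 2 days, onset date used | 0.999 | 1.8% | 2.8% |

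The effect is small, needs delays that differ by case status, and can go either way. Doses given between onset and test were not simulated.

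**Last doses pooled, dose number not in the model**

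| VE for doses 1/2/3 | OR per 30 days | False waning | False strengthening | OR with dose number added |
|---|---|---|---|---|
| 40/40/70% | 1.044 | 45% | 0% | 1.000 |
| 40/50/70% | 1.024 | 16% | 0% | 1.000 |
| 40/55/70% | 1.011 | 7% | 0.7% | 0.998 |
| 40/70/70% | 0.962 | 0% | 34% | 0.999 |

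Over 180 days the extremes amount to 1.044^6 = 1.29 and 0.962^6 = 0.79 on the odds ratio, with no true change in protection. With dose number in the model, false waning falls to 1.5–4%.

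**A second dose mix, period 2 only.** The assumptions were 12% unvaccinated, 48% with two doses at 100–225 days (VE 40%), and 40% boosted at 0–90 days (VE 40% before day 14, then 65%). In a very large sample (n = 600,000) a pooled linear time term fits VE of about 61%, 49% and 33% at days 14, 120 and 225, although neither dose wanes. At 1,728/2 = 864 patients, false waning was significant in 58–69% of 500 runs, for baseline log-odds of 0 to 0.9. With dose number added it was significant in under 1%. A single slope then still showed false strengthening in 8–12% of runs, because it absorbs the booster's rise over its first two weeks. That is a reason for time bands or a spline.

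**The case against.** The strongest reply is that unadjusted pooling is not what the article says. Number of doses is collected and named as a potential confounder, and the regression is to use the covariates described. If dose number is in the time model, the pooling artefact largely disappears. This stands, and it makes the text unclear rather than wrong on that point. It does not settle the matter, because the stratification list omits dose number and the three sentences on the time analysis do not mention it.

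The reversed subtraction is very probably a slip. The Results section shows the intended direction, and a column of negative times would be noticed. That also stands, but the stated definition is still wrong and costs one phrase to correct.

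The onset-to-test gap is capped at 10 days, against times since vaccination of months, so the numerical bias is usually small. This stands too. The better argument for onset is that a dose given after onset should not count.

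A reader might also infer that the plan fits one linear term that cannot follow a rise and then a decline in protection. The text does not support that. It says continuous, which a spline also satisfies, and an article may leave functional form and the coding of the unvaccinated to a fuller document. In the first simulation set-up, with equal VE for all doses and no waning, the linear form gave false waning at the nominal 2.5%.

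**Conclusion.** The point holds in a limited form.

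- The order of subtraction is wrong as stated. It inverts a real slope. A reader might infer that it produces waning from nothing, but it does not: with no waning the reversed variable gives 1.000.
- Ending at the test is the weaker choice when onset date is available. Its numerical effect is small (0.985 to 1.016 per 30 days under the differential delays assumed).
- The substantive issue is the unstated handling of dose number. If it is left out, the slope mixes booster benefit with waning, and the bias can go in either direction: 1.044 to 0.962 per 30 days across the VE patterns tried in the first dose mix.

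Those sizes rest on assumed dose mixes, time ranges, delays and VE by dose. They show mechanism and direction, not a forecast for this study. It would be too strong to say that the planned analysis will show false waning, or that the main results are affected. This is a subsequent analysis, and the main VE estimate does not use the variable. It should be corrected before the waning analysis is run, but it is not a critical flaw in the study.

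**What to change.** Replace the definition with: time since vaccination = symptom-onset date minus the date of the last dose given before onset. Doses given on or after onset do not count.

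Then state that:

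- VE by time is estimated separately for primary series and booster, or at least adjusted for number of doses.
- Every estimate uses the same unvaccinated reference group.
- Time enters as bands (for example under 14, 14–90, 91–180 and over 180 days) or as a spline. The early days after a dose should be separated from the later period.

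Add number of doses to the stratification list so that it agrees with the list of potential confounders.

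The article already plans to use onset date, vaccination date and number of doses. The change is therefore one of analysis wording, provided the date of each dose is recorded for patients whose latest dose followed onset. The statistical cost is a few more parameters and somewhat wider intervals per dose group or band.

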## 3. Results

On the 14 May 2022, the data collection was still ongoing, and it is expected to be completed by June 2022. A preliminary analysis is going to be performed after finishing data collection. Currently, we have obtained data on 1329 eligible patients (652 cases and 677 controls) for both periods of the study and we plan to increase the number by 30%. We expect to obtain a vaccine effectiveness of between 40 and 70% in the prevention of symptomatic infection and 70 and 90% in the prevention of severe cases of COVID-19, according to previously described results. It is anticipated that this effectiveness may be lower in more advanced age groups due to a less-robust response of the immune system in these individuals. Additionally, we expect lower vaccine effectiveness in unvaccinated or partially vaccinated people, particularly in people with moderate-to-severe COVID-19. As the waning of VE has been previously reported [36], we believe that VE will be lower in people vaccinated with their last dose first. However, data analysis will allow us to confirm this. The results will be disseminated in national and international scientific journals in 2022–2023.

## 4. Discussion

This project aims to evaluate the effectiveness of vaccination against COVID-19, to produce scientific evidence that can support strategies for the prevention and control of pandemics. This might contribute to the planning of more suitable vaccination campaigns and to tackle phenomena such as vaccine hesitancy [37].

This will be the first study to evaluate the real-world effectiveness of the vaccination campaign against COVID-19 in people over 18 years old in Portugal. The study design described has important advantages, namely: (1) the cases and controls are selected in the same health care unit and, therefore, probably residing in the same geographic area and in the same sociocultural environment, reducing bias due to risk variation according to the location [2]; (2) cases and controls all sought care for COVID-like illness, which reduces the likelihood of bias related to seeking health care or testing, which is an advantage compared to traditional case control and cohort studies [2,27,29]; (3) the vaccination status is usually recorded before performing the test, prior to the knowledge of the result, so that a potential bias of differential misclassification of exposure is avoided [2].

As with other observational studies, this study may have limitations in internal validity that we will try to control in the study design and data analysis.

Vaccinated individuals may have more risk behaviours because they believe they are protected, resulting in underestimation of the vaccine effectiveness [2]. Furthermore, it will not be possible to directly measure vaccine effectiveness against specific variants due to the low proportion of genotyped cases. However, periods in which different variants were dominant will be analysed so that an approximation of vaccine effectiveness against these variants can be achieved, indirectly.

Confounding may occur when the vaccination status is associated with a person’s risk of being exposed to SARS-CoV-2. If, for example, people who choose not to be vaccinated are also those who do not adhere to individual protection measures, this can lead to an overestimation of vaccine effectiveness.

It is also worth noting that participants in research with test-negative designs are limited to those who use health-care services. The National Health Service in Portugal is universal, general and tendentiously free of charge. Although undocumented migrants or refugees may use public healthcare services, they may avoid going to hospitals because of fear or language barriers and will be at higher risk for serious illness in general than other people; this limits the generalizability of the findings to the disadvantaged groups that could not be represented in our study.

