As of 10 March 2022, Portugal had over three million cumulative laboratory-confirmed cases of SARS-CoV-2, emerging from five waves of infection, as can be seen in Figure 1 [15]. Delta variant (B.1.617.2) appeared in India in December 2020 and rapidly spread worldwide, becoming dominant by August 2021 in Portugal. It has been shown to be more transmissible and virulent than the Alpha variant [16]. Additionally, a study performed in Portugal showed significantly higher odds of vaccine breakthrough infection in Delta-infected patients than in Alpha-infected, suggesting lower effectiveness of the mRNA vaccines in preventing infection with the Delta variant [17], which is consistent with other studies [18,19].

The B.1.1.529 (Omicron) variant was first found in South Africa in November 2021, and it quickly spread worldwide. Omicron variant was shown to be 2.8-times more infectious than the Delta [20] and was responsible for the fifth pandemic wave in Portugal, which reached its peak on the 25 January 2022 with 5598 cases per million inhabitants. Omicron has shown immunity escaping capacity in laboratory studies and booster vaccine doses may be essential to overcome this [21,22].

This article presents the study protocol for evaluating the effectiveness of vaccines against COVID-19 in the prevention of symptomatic and severe disease in a district located in the northern region of Portugal, using a retrospective test-negative case–control design.

We will perform a comparative analysis between the fourth pandemic wave (1 June to 30 September 2021), dominated by Alpha and Delta variants and the fifth pandemic wave (1 November 2021 to 2 March 2022), Omicron-dominant, represented in Figure 1. In the beginning of the first period, the Alpha variant was dominant in Portugal, and by the week of 21 to 27 June 2021, the Delta variant became dominant [23]. The fifth wave of infection in Portugal, corresponding to our second period in analysis, was dominated by the Omicron variant since the week of 20 to 26 December 2021 [24].

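### The two-period contrast is offered as an indirect variant comparison, but time since last dose shifts sharply between the periods and is not built into that contrast

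*Protocol article*

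**What the plan says.** The Introduction (section 1) sets up the comparison: the "fourth pandemic wave (1 June to 30 September 2021), dominated by Alpha and Delta variants" against the "fifth pandemic wave (1 November 2021 to 2 March 2022), Omicron-dominant". Section 2 repeats it: "The results will be compared in two periods". The Discussion (section 4) concedes that few cases were genotyped and then states the purpose of the contrast: "periods in which different variants were dominant will be analysed so that an approximation of vaccine effectiveness against these variants can be achieved, indirectly".

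Section 2 also gives the pace of vaccination: "being 50% of people fully vaccinated by 20 July 2021", and "on the 22 September 2021, Portugal was the first country in the world hitting the milestone of 85% of the population fully vaccinated".

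On the timing and number of doses, section 2 does three things. It lists vaccination date, vaccine type and number of doses among the baseline variables to be examined as potential confounders. It includes vaccination date and vaccine product, but not number of doses, in the list of stratification variables. It then adds: "In a subsequent analysis, the vaccine effectiveness will be evaluated by the time since vaccination", with time as a continuous variable. It does not say how that later analysis relates to the comparison of periods.

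Elsewhere the article accepts that effectiveness wanes (section 3) and that boosters may matter against Omicron (section 1). The limitations in section 4 name neither as an alternative explanation for a difference between periods.

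**The concern.** A difference in effectiveness between two calendar periods can be read as a variant difference only if vaccinated people in the two periods are otherwise comparable in how they were vaccinated. The roll-out ran through the middle of the first period and had passed 85% before the second began. Unboosted vaccinated patients in the second period are therefore mostly much further from their last dose, and others will have had a booster. Waning and boosting then travel with the variant.

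The Conclusions (section 5) offer the results for decisions on both booster doses and variant-specific formulations. Loss of protection with time bears mainly on the first and immune escape mainly on the second. A pooled period difference cannot tell them apart.

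**Working it through.** The plan states no figure for this point, so there is none to reproduce. The check is date arithmetic, a reading of what the listed adjustments can do, and an illustration.

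**1. Inputs from the article.** Period 1 is 1 June to 30 September 2021, as in section 1 (section 2 prints 31 September, which does not exist). Period 2 is 1 November 2021 to 2 March 2022. Each lasts 122 days. The midpoints are 31 July and 31 December 2021. Full vaccination reached 50% by 20 July and 85% on 22 September 2021.

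**2. Days since completing the primary series, if not boosted.**

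| Completed on | Period 1 midpoint | Period 1 end | Period 2 start | Period 2 midpoint | Period 2 end |
|---|---|---|---|---|---|
| 20 July 2021 | 11 | 72 | 104 | 164 | 225 |
| 22 September 2021 | not yet | 8 | 40 | 100 | 161 |

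The shift between midpoints is 164 − 11 = 153 days. Anyone who had completed by 22 September and was not boosted is at least 40 days out throughout period 2 and at least 161 days out at its end.

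**3. Whether the listed adjustments remove the shift.**
- *As covariates.* An unvaccinated person has no vaccination date, and a dose count of zero simply restates being unvaccinated. These variables subdivide the exposure. They are not characteristics shared by vaccinated and unvaccinated people, so adjusting for them does not put the two period estimates on a common footing.
- *As calendar-date strata.* Take all last doses given in July 2021. In period 1 they are at most 91 days old (1 July to 30 September). In period 2 they are at least 93 days old (31 July to 1 November). Within that stratum the two periods share no value of time since dose, so stratifying by calendar date preserves the imbalance.

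**4. Illustration with no variant effect.** Let r be effectiveness soon after a dose and w after waning, the same in both periods. Let f be the waned share of the vaccinated in period 1 and b the boosted (recently dosed) share in period 2.

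VE₁ = (1 − f)·r + f·w; VE₂ = b·r + (1 − b)·w.

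Take r = 70% and w = 40%, the ends of the range that section 3 expects for symptomatic infection. The shares f and b are assumptions, because the article gives none.

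| f | b | VE₁ | VE₂ | Fall (points) |
|---|---|---|---|---|
| 0.10 | 0 | 67% | 40% | 27 |
| 0.10 | 0.30 | 67% | 49% | 18 |
| 0.10 | 0.60 | 67% | 58% | 9 |
| 0.30 | 0 | 61% | 40% | 21 |
| 0.30 | 0.30 | 61% | 49% | 12 |
| 0.30 | 0.60 | 61% | 58% | 3 |

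With w = 50% over the same shares, the fall is 2 to 18 points. In general, VE₁ − VE₂ = (r − w)(1 − f − b). The artefact is zero when b = 1 − f and changes sign above that, for example at b above 0.70 when f = 0.30.

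**5. A related mixing.** The second period "was dominated by the Omicron variant since the week of 20 to 26 December 2021". The 49 days from 1 November to 19 December, out of 122, precede that week, so even the period label is an imperfect marker of variant.

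**The case against.** The best defence is that the plan does more than a quick reading suggests, and much of that defence stands.

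- A reader might infer that booster status is postponed to the later analysis. It is not: only time since vaccination is. Number of doses is a listed potential confounder, and vaccination date is both a listed confounder and a stratifier.
- A reader might infer that a single vaccination odds ratio will be produced for each period. The article nowhere says so. It describes adjusted models, stratified odds ratios and interaction tests.
- A reader might say that the plan simply equates the period difference with a variant effect. The wording is softer, claiming only an indirect approximation, and it sits among the limitations. In context, however, that hedge concerns the shortage of genotyped cases. It does not warn that waning or boosting could produce the difference.
- The article is silent on whether the time-since-vaccination results will also be compared by period, and silence is not exclusion. A full analysis plan may define the exposure levels. Their absence from a condensed article is therefore not the point. The point is that the article states an inference that the adjustments it describes do not support.
- The coverage figures are national and cover the whole population, whereas the study takes adult emergency patients in one district. The campaign began on 27 December 2020, so some vaccinated patients were already months past their dose in period 1. This limits any statement about shares, but it does not remove the shift in time since dose for a given vaccination date.

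**Conclusion.** The concern holds in a limited form. Section 4 offers the two-period contrast as an indirect guide to effectiveness by variant, while time since the primary series differs sharply between the periods on the article's own dates: 153 days between midpoints for an unboosted person vaccinated on 20 July. The deferred analysis is not tied to the contrast, and the listed confounders and strata do not make the two estimates comparable. Waning alone could therefore produce a difference that would be taken as variant-related.

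That conclusion rests on the stated dates and on waning, which the article itself accepts. The size does not follow from the documents. The 3 to 27 points depend on assumed effectiveness values and on assumed waned and boosted shares. A reader might want to quote one figure as the expected bias, or to treat a spurious fall as certain. Neither is supported: the article gives no booster coverage, and high uptake in period 2 could cancel the artefact or reverse it. That booster uptake differs between the periods is plausible, but it is not quantified.

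**What to change.** Before the analysis:

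1. Define exposure by dose category (including booster) crossed with a few broad bands of time since last dose, each against the unvaccinated, with the bands fixed in advance.
2. Compare periods only within the same exposure level. Where a level has no patients in one period, or too few to estimate, say that no contrast is available there.
3. In section 4, name waning and boosting as rival explanations for any difference between periods, and do not attribute the pooled difference to variant. Carry the same restraint into the statements on boosters and variant-specific formulations in section 5.

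Vaccination dates and dose numbers are already among the data to be collected, so the change affects only analysis and wording. The price is precision: 1,329 patients, planned to rise by 30% to about 1,728 (1,329 × 1.3), would be divided among more contrasts. Intervals will widen and some levels may be empty. That is why the bands should be few and broad.
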